## Abstract

**Background:**

Mental illness among Malaysian children is gradually reaching a fundamentally alarming point as it persistently shows increasing trend. The existing literature on the etiologies of children’s mental illness, highlights the most common cause to be ineffective or impaired parenting. Thus, efforts to combat mental illness in children should focus on improving the quality of parenting. Documented interventional studies focusing on this issue, particularly in Malaysia, are scarce and commonly report poor treatment outcomes stemming from inconvenient face-to-face instructions. Consequently, proposing an accessible online and digital-assisted parenting program is expected to reach a larger number of parents, as it can overcome substantial barriers. Hence, this study aims to develop a universal digital-assisted preventive parenting intervention called DaPI, that aims to enhance mental health of children in Malaysia.

**Methods:**

A total of 200 parents of children aged 10–14 years will be recruited and randomized into two groups either intervention or waitlist-control based on a 1:1 ratio for a duration of 8 weeks. Those in the intervention group will receive eight sessions of the DaPI program that focus mainly on parenting and children’s mental health. The primary outcome of this study will essentially focus on the changes in parent-reported parenting behavior and parental self-efficacy. The secondary outcome will be changes in children’s mental health (i.e., behavioral problems and emotional maladjustment). Assessments will be arranged pre- and post-intervention as well as at the 1-month follow-up. Analyses will be conducted using a paired *t*-test and multivariate analysis of covariance.

**Discussion:**

The expected outcome will be the establishment of DaPI in promoting children’s mental health by targeting changes in parenting behavior and parental self-efficacy in Malaysia. Findings from this study will be beneficial for policymakers to invest in parenting programs that could provide support to parents in enhancing their child’s overall development.

**Clinical trial registration:**

[www.irct.ir], identifier [IRCT20211129053207N1].

## Introduction

### Background

The dramatic rise of mental health problems among the younger generation in Malaysia is drawing great concerns from various societal groups, particularly parents, educators, researchers, and community leaders for its potential detrimental impact on the nation’s socio-economic development (IPH, 2017). Depression, anxiety, stress, and disruptive behaviors are typical mental health problems that are seen in children. These problems can develop as early as 10 years-old and can be evident as children go through the stages of childhood development. It is thus, important for parents to be aware of the symptoms of mental health problems in children and to seek immediate treatment. Untreated childhood mental health problems can evolve into major mental disorders that can persists into adulthood thereby affecting an individual’s adult life.

To combat this rising issue of mental health problems in Malaysian children, preventive and interventional strategies need to be implemented. Parenting programs would have the potential to both prevent and reduce the risk of mental health problems in children. Developing effective parenting programs requires efficient frameworks to be in place (Bowlby, 1969; Bandura, 1977; Belsky, 1984; Baumrind, 1991) that target changes in parenting practices to promote desirable child outcomes (Sanders and Kirby, 2015; Baker, 2016). Intervention programs for parents can vary from universal to selective or even indicated prevention (Leslie et al., 2016; Lindsay and Totsika, 2017). Universal intervention is offered to all parents seeking improvement in parenting practices or those in need of support, regardless of the risk level. Selective intervention targets parents of children who are at high risk and have not been referred to a clinic. The indicated intervention serves parents of children who have been referred to clinics to seek professional help for their mental health problems.

Despite evidence of the effectiveness of parenting programs, engaging parents and retaining them in the programs is a challenge. Parent attendance rates have been shown to vary depending on numerous factors, from scheduling (Shenderovich et al., 2018) to parental stress (Chacko et al., 2017) and their attitude (Ozbek et al., 2019). As these interventions are traditionally conducted face-to-face, parents may find it challenging to commit and engage in weekly sessions because of difficulty in balancing personal, family, and work life. Advancements in technology have enabled intervention research in the Western society to utilize digital-assisted (e.g., computers, smartphones, tablets, and the Internet) interventions to increase parents’ adherence to parenting programs. Furthermore, digital-assisted intervention helps in expanding the reach of a given treatment by allowing parents to access parenting programs at their own convenience regardless of their location and reduces resources required in implementing such programs (Hansen et al., 2019).

Parenting intervention research to encourage children’s development is rare in Malaysia, and is further scarce on mental health. A few prior studies (e.g., Mohamed and Hussin, 2015; Ahmad et al., 2018) have designed research programs mainly *via* face-to-face interventions either at home or at a clinic. Nonetheless, a study used social media to support face-to-face interventions in their parenting program to reduce obesity in children (Ahmad et al., 2018). Ahmad et al. (2018) in their study revealed that adherence was higher among parents participating in social media than among those participating in traditional face-to-face sessions. This implies that Malaysian parents are becoming more adherent to digitally assisted interventions compared to the traditional approach.

### Mental health in children

Mental health problems in children, especially in those aged 10–14 years, are becoming more prevalent (IPH, 2020). Generally, the common mental health problems reported in children can be categorized into behavioral (e.g., antisocial and conduct behavior), developmental (e.g., autism and global developmental delay), and emotional disorders (e.g., depression and anxiety) (Gould, 2016). The Malaysian National Health Morbidity Survey reported that the general prevalence of mental health problems among children aged 5–15 years was 12.1% (IPH, 2015). The survey further revealed that the prevalence of mental health problems caused by peer-related problems (32.5%) was the highest, in contrast to conduct problems (16.7%), emotional problems (15.7%), prosocial skills (11.2%), and hyperactivity (4.6%) (IPH, 2015). In 2017, a survey (IPH, 2017) showed that anxiety (39.7%) had the highest prevalence, unlike depression (18.3%) and stress (9.6%) for children aged 13–17 years. Anxiety is thus a more predominant mental health problem among Malaysian school-going children than depression and stress.

Children suffering from mental health problems pose longstanding consequences for families, society, and the country at large. In most cases, children’s mental health problems go undetected or unacknowledged and are left without any intervention. This increases the risk of growing up and developing an array of difficulties involving and not limited to personal and family relations; academic achievement; and emotional, physical, and behavioral health (Sheehan, 2017). If mental health problems in children are unsuccessfully managed, they persist throughout their adult lives. For example, persistent and recurrent depression and anxiety in children may manifest as a major depressive disorder or generalized anxiety disorder (DSM-5; American Psychiatric Association, 2014). It is clear that early childhood intervention in mental health is essential for ensuring children’s optimal development. Given the increase in prevalence and societal concerns regarding children’s mental health problems, research has begun to focus on developing effective early prevention programs to curb mental health problems in children. As parents are salient figures throughout the developmental stage of their children, improving parenting practices will help enhance their mental health (Melchior and van der Waerden, 2016).

### Digital parenting intervention for children’s mental health

Emerging research has suggested the use of digital-assisted interventions to address various barriers in parenting interventions (Flujas-Contreras et al., 2019; Hansen et al., 2019; Harris et al., 2020; Hamdani et al., 2021; Peyton et al., 2022). Digital-assisted interventions show great potential in fostering the mental health of a community due to better reach and efficiency of mental healthcare delivery. Smartphone apps, short message services (SMS), social media, and interactive websites are widely utilized to support behaviors involved in prevention, self-management, and delivery of evidence-based mental health care practice (Stawarz et al., 2019; Marshall et al., 2020; Hamdani et al., 2021). In comparison to conventional face-to-face intervention, digital-assisted intervention allows treatment and services to be more accessible to parents, anytime and anywhere, and are available 24/7 upon demand to suit parents’ schedules (Baumel et al., 2016).

Digital-assisted parenting interventions delivered online may be self-directed (where parents complete a program without any assistance from a practitioner) or may provide guidance and support from a practitioner *via* various methods (i.e., phone calls, video conferencing sessions, or text messages and emails). Whether self-directed or assisted, both provide clear benefits for parents. Nevertheless, parents in self-directed online intervention may not be able to practice parenting skills learned in front of a practitioner, nor have their progress throughout the program, reviewed. In view of such setbacks, recent online interventions have begun to include some form of practitioner support and are not fully self-directed in nature (Tully et al., 2017). Despite the effectiveness and acceptability of various types of digitally assisted interventions established in Western culture, such interventions specifically related to parenting and children with mental health issues in the Malaysian context are yet to be established. Moreover, the few available interventions have focused on limited developmental aspects (e.g., reducing obesity) (Ahmad et al., 2018) rather than mental health. Furthermore, in this context, only a study by Ahmad et al. (2018) utilized social media alongside traditional face-to-face interventions. They reported that among 122 parents, the majority participated better through social media (96.9% WhatsApp and 81.3% Facebook) compared to face-to-face sessions (42.2 and 68.8%, respectively). This suggests that Malaysian parents with young children are more likely to favor digitally assisted interventions that are more easily accessible to them than traditional methods of interventions.

In recent years, the pattern of digital usage among Malaysians has increased steadily. In its latest report, the Malaysian Communication and Multimedia Commission (MCMC; 2020) indicated that a vast majority (88.7%) of Malaysians utilized the Internet daily, spanning over a period of 1–4 h (32.9%). The highest number of Internet users were males (54.3%) and those in their 30 s (25.9%) and 40 s (17.9%), who, on average, spent a longer time (i.e., between 5.9 and 7.3 h) on the Internet daily. A majority (88.6%) of Malaysians used the Internet at home, while 68.1% tended to use the Internet while on-the-go, and slightly more than half (56.4%) of the users accessed the Internet at the office. Malaysian users were found to use smartphones (93.1%) when accessing the Internet, followed by laptops (44.2%), desktops (28.1%), and tablets (20.4%). The online activities frequently performed by Malaysians were mainly communication (96.5%), visiting social networking platforms (85.6%), and acquiring information (85.5%). Given the encouraging figures of Internet usage by Malaysians, an online digital-assisted parenting program would most likely be a more promising platform for Malaysian parents to receive parenting education and skills in encouraging a positive mental health of their children.

As parents are active agents in influencing child development, their participation in parenting intervention programs would encourage improvement in parenting and consequentially reduce behavioral and emotional problems in children. Considering the significant contribution of parents in child development and emerging preference for digital-assisted intervention, this paper presents a protocol for a universal, digital-assisted preventive parenting intervention called “DaPI,” with the aim of supporting Malaysian parents in promoting their children’s mental health.

### Objective

The overarching aim of this study is to determine whether a universal, digital-assisted preventive parenting intervention named DaPI will be effective in promoting the mental health of children by targeting parenting behavior and parental self-efficacy. We hypothesized that parents in the DaPI program would report lower rates of ineffective parenting behavior and higher parenting self-efficacy (primary outcomes), which would lead to improved mental health in their child (secondary outcomes, i.e., better behavior and emotional adjustment).

## Methods and analysis

### Trial design

This study is a randomized controlled trial (RCT) of the DaPI online program. Interested Malaysian parents with children aged 10–14 years will be randomly assigned to either the intervention group (DaPI) or waitlist control (WLC) group. This study will experimentally evaluate the relative impact of DaPI and WLC on parenting and child outcomes. The SPIRIT (Standard Protocol Items: Recommendations for Interventional Trials) guidelines for RCT were used in this study.

Self-reported data will be collected at three time points (pre- and post-intervention and 1-month follow-up). Parents will need to sign an online consent form before completing the pre-intervention (baseline) questionnaire on enrollment in the study. Parents will be able to access the online program at their own pace throughout the span of 8 weeks and then complete a post-intervention questionnaire. Parents will complete the follow-up questionnaire a month after answering the post-intervention questionnaire.

### Eligibility criteria

Eligible participants will be parents of children aged 10–14 years who are currently living in Malaysia. We aim to recruit 200 parents to participate in the study. Parents from the same household can participate if they focus on a different child within the stipulated age range. It would be an added value to the household if both parents took the opportunity to upgrade their parenting knowledge and skills to improve their children’s development. The inclusion criteria for parents receiving the DaPI would be to have a child within the specified age range and can understand the Malay language. In terms of exclusion criteria, parents who specified that they are currently receiving professional help for their child’s mental health problems will be excluded. No other screening assessments for inclusion or exclusion of the DaPI program will be conducted.

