### Participants

#### Randomization

Participation randomization to either the DaPI or WLC group will be overseen by a research coordinator. Using a simple random technique, each participant will be assigned a unique identification number generated by a random number generator in a 1:1 proportion. Immediately after the participants completed the pre-intervention questionnaire, the research coordinator will notify them of their allocation *via* email.

Participants in the DaPI group will get immediate access to the online program, by logging in with their user ID and password provided by the researcher. They will be able to access the program as per their convenience particularly, their chosen time and day. Meanwhile, participants in the WLC group will be given access to the program after the 1-month follow-up questionnaire has been collected. Figure 1 summarizes the flow of participants in this study. Due to the nature of the intervention, participants and researchers directly involved in the online intervention cannot be blinded to the allocation. Nonetheless, researchers involved in data collection and the analyses will be blinded, as they are not involved in participant allocation or online intervention.

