#### Intervention

DaPI is an adaptation of established evidence-based Western parenting programs, such as Parenting Wisely (Gordon, 2003), Triple-P Positive Parenting Program (Sanders et al., 2000), and the Incredible Years (The Incredible Years, 1984), that focused on parental factors associated with children’s mental health in Malaysia. Considering the diverse ethnicity and religious culture of Malaysia, a parenting module incorporating culturally specific parenting beliefs with local examples would be more suitable for Malaysian parents. As emphasized in previous literature (Hong et al., 2012; Keshavarz et al., 2013; Andrew, 2019; Zulkefly et al., 2021), the parenting beliefs of Asian parents differ from those of the Western construct. For example, Western parents view authoritarian parenting as negative, harsh, and more likely to yield negative outcomes for children. Contrastingly, Asian parents view an authoritarian style as positive style of parenting, where they show care, concern, and involvement through firm control and governance of the child. Furthermore, Asian parents also expect their children’s filial piety and obedience to their families. Contrary to their counterparts from the West, children of authoritarian parents show positive outcomes and feel warmth and care through their parents’ control and firm parenting behavior. Therefore, adjustments and adaptations are needed when using Western programs in the Asian context.

The DaPI can be completed online using a computer, tablet, or smartphone at any time, which is convenient for the parents. The interactive online program will consist of various materials including written information, pre-recorded videos, audio, interactive quizzes, and family activities across the eight sessions. Table 1 presents an overview of each session in the DaPI. The DaPI program will be conducted in Malay, the official language of Malaysia, and will use examples and pictures that represent Malaysian local culture.

**TABLE 1 T1:** Sessions content.

Session number and title	Content overview
1. Normal development and challenges in early adolescence	• Developmental characteristics of early adolescents. • Developmental challenges of early adolescents.
2. Parent-child attachment	• Role of parent-child attachment in child mental health development. • Principles of building secure parent-child attachment relationship.

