#### Control

Participants in the WLC group will receive no treatment and will continue with their usual parenting practices in managing their children. After a 1-month follow-up, the participants will be given access to the DaPI program.

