#### Outcome measures

Parents in both the DaPI and WLC groups will complete a questionnaire comprising the following questions at pre- (baseline) and post-intervention (8 weeks) and at the 1-month follow-up mark. Parents in the DaPI group will be allowed to complete the questionnaire, regardless of whether they have completed all eight sessions of the DaPI program. Prior to answering the questionnaire, parents with more than one child within the required age range will need to select a child as the focus of the study. If both parents in the same household wished to participate, they would choose a different focus child within the stipulated age range. The questionnaire will be administered in Malay. A forward backward translation procedure will be conducted for questions that have not been translated and validated in a Malaysian sample.

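### Both parents of a household may enrol but are randomised individually, so about half of such pairs are expected to be split between DaPI and waitlist, with a risk of spillover into the control arm

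*Protocol article*

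**What the plan says.** Eligibility criteria in the protocol article allows co-enrolment, "Parents from the same household can participate if they focus on a different child within the stipulated age range", and encourages it: "It would be an added value to the household if both parents took the opportunity to upgrade their parenting knowledge and skills". Outcome measures repeats the rule: "If both parents in the same household wished to participate, they would choose a different focus child within the stipulated age range".

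Randomization makes the individual the unit of allocation: "Using a simple random technique, each participant will be assigned a unique identification number generated by a random number generator in a 1:1 proportion". No household unit, stratum or linking rule is mentioned. Each participant learns the result by email straight after completing the baseline questionnaire.

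On the comparator, Control says: "Participants in the WLC group will receive no treatment and will continue with their usual parenting practices in managing their children". Access follows only after the 1-month follow-up.

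On content, Intervention lists "interactive quizzes, and family activities across the eight sessions", and Table 1 has sessions on effective communication (3), family cohesiveness (5) and family conflict (6).

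The sample-size section asks for 128 parents (d = 0.50, alpha 0.05, power 0.80) and sets a target of 200. It makes no allowance for spillover within households.

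**The concern.** The eligibility rule and the allocation rule do not fit together. If two parents under one roof are allocated separately, one can be in DaPI while the other waits about 12 weeks as a control. Part of the programme is aimed at the family as a whole, so it can reach the waiting parent without a login.

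The secondary outcome is the more exposed. The waitlist parent rates a focus child who lives with a parent taking DaPI, so that child may be affected even if the waitlist parent changes nothing. Requiring a different focus child stops two parents rating the same child, but it does not stop exposure.

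Spillover of this kind would improve the control arm and shrink the estimated effect. Because it arises at allocation, a later analysis plan could not reliably remove it.

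**Working it through.** **1. The plan's own figure.** A two-sided two-sample t-test with d = 0.50, alpha 0.05 and power 0.80 needs 63.77, so 64 per arm and 128 in total. This matches the protocol exactly. Power at 64 per arm is 80.1%.

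**2. Probability that a pair is split.** Under independent 1:1 allocation it is 0.5. With arms fixed at 100 and 100 it is 100/199 = 0.5025.

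**3. Share of the waitlist arm with a DaPI partner.** Let s be the share of participants who enrol as one of a pair. The share is s/2. For example, s = 0.20 of 200 parents is 40 parents, or 20 pairs. About 10 pairs are split, so about 10 of 100 waitlist parents have a partner in DaPI.

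**4. Dilution.** Let c be the fraction of the DaPI effect that passes to the waitlist partner. Then

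d_eff = 0.50 × (1 − s × c / 2).

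The documents give neither s nor c, so every row below is an assumption. Power is at 64 per arm.

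| s | c | d_eff | Power | Total N for 80% power |
|---|---|---|---|---|
| 0.05 | 0.5 | 0.50 × (1 − 0.0125) = 0.494 | 79.2% | 132 |
| 0.20 | 0.5 | 0.50 × (1 − 0.05) = 0.475 | 76.0% | 142 |
| 0.20 | 1.0 | 0.50 × (1 − 0.10) = 0.45 | 71.4% | 158 |

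A simulation of the second row (within-household correlation 0.3, 20,000 runs) gave a mean effect of 0.475 and power of 75.9%, in agreement with the formula.

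**5. Does ignoring the pairing distort the test under the planned allocation?** Positively correlated parents in the same arm increase the variance of the group difference, and split pairs reduce it. With each case about equally likely, the two cancel on average. Simulated type I error of a t-test that ignores pairing (N = 128, 20,000 runs, s from 0.2 to 1.0, correlation 0.3 or 0.5) was 4.9% to 5.2%.

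**6. Household allocation.** All pairs are then in one arm and the cancellation is lost. The design effect is 1 + ρ × s, where ρ is the within-household correlation. With ρ = 0.3 and s = 0.20 it is 1 + 0.06 = 1.06, and 128 × 1.06 = 135.7, so N = 136. Over s from 0.05 to 0.40 and ρ from 0.1 to 0.5 it runs from 1.005 (N = 129) to 1.20 (N = 154). If households are allocated as units but pairing is ignored in the analysis, simulated type I error is 5.6% to 7.3% for s from 0.2 to 0.4.

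**The case against.** The strongest reply is that the problem may be very small. A pair needs two willing parents who both understand Malay and at least two children aged 10–14, which probably keeps s low. Login is by personal user ID and password, the psychologist's feedback concerns the enrolled parent's own activities, and the primary outcomes are the respondent's own parenting behaviour and self-efficacy. Full spillover would mean that a parent who never logs in gains the whole effect of eight sessions. Any bias is also toward no effect, so it would not create a false positive. All of this stands. It is why the range begins at a loss of under one point of power and why the full-spillover row is only an upper bound.

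A reader might go further and infer that the control arm will be contaminated, or that the Control section is contradicted. The documents do not show this. That section describes what the waitlist group is given, and spillover is a plausible risk rather than a documented event.

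A reader might also infer that treating the two parents as independent makes the standard errors or the type I error wrong. Step 5 shows that under individual allocation it does not do so materially. The condensed statistics paragraph names MANCOVA without a household term, but an article may leave such a term to an analysis plan that is not shown.

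The split allocation itself is not answered by any of this. Co-enrolment is actively encouraged, and nothing in the article keeps a household together.

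**Conclusion.** The point holds as a design weakness of uncertain and possibly small size. Joint enrolment with individual 1:1 allocation is expected to split about half of co-enrolled pairs. In split households the waitlist parent, and more so that parent's focus child, is at risk of spillover that pulls the contrast toward no effect.

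On the assumptions shown, d falls from 0.50 to between 0.494 and 0.45, and power at 64 per arm from 80.1% to between 79.2% and 71.4%. These figures depend entirely on an assumed pairing rate (5% to 20%) and an assumed spillover (half to full). The conclusion does not extend to the validity of the test under the planned individual allocation, where type I error stays at about 5%.

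**What to change.** There are two options, and either must be in place before enrolment.

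**Allocate by household.** Record a household identifier at enrolment. Where both parents wish to join, have both consent and complete baseline before either is allocated, then make one allocation for the household. Accept no second parent once the household's arm is known. Under the current procedure the arm is emailed right after baseline, so a partner who joined later and inherited that arm would decide to enrol, and answer baseline, already knowing it. That would break allocation concealment. Analyse with a household random effect or cluster-robust standard errors, which household allocation makes necessary (step 6). The cost is a design effect of about 1.06 (N about 136 instead of 128) at 20% in pairs and a correlation of 0.3, plus some coordination at enrolment. The main gain is the removal of the bias, not of the power loss: at N = 128 on these assumptions power is 77.8%, against 76.0% for individual allocation with half spillover.

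**Enrol one parent per household.** The required N stays at 128 and no clustering arises. The cost is fewer eligible parents and the loss of the joint participation that the protocol values.
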